### **11.2. Insertion of left ventricular assist devices**

The insertion of a left ventricular assist device is typically performed according to the recommendations of the American Heart Association and the Korean Society of Cardiology when drugs are not effective. However, in exceptional cases such as myocardial infarction with left ventricular wall motion abnormalities that are expected to result in cardiac arrest, the decision to insert IABP and ECMO more aggressively is left to the discretion of the operator. After the insertion of a left ventricular assist device, anticoagulant therapy should be administered to prevent thromboembolism unless it is contraindicated, and in order to prevent limb ischemia, the insertion of a catheter for limb perfusion is recommended if there is no palpable doppler signal or a change in limb color is detected. If pulmonary edema and pulmonary hemorrhage occur due to left ventricular dilatation after ECMO insertion, percutaneous or surgical decompression is recommended.

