## **9. Inclusion criteria, exclusion criteria, and targeted sample size and their basis**

### **9.1. Inclusion criteria**

1. 19 years old or older
- 2-1). Systolic blood pressure is less than 90mmHg for more than 30 minutes despite the fluid therapy, or Use of pressure boosting agents is necessary.
- 2-2). Peripheral hypoxia (cold skin, urine less than 30 cc per hour, impaired consciousness, lactate  $\geq 2.0$  mmol / l) or a person with pulmonary edema.
3. Causes of cardiogenic shock include acute myocardial infarction (including in coronary intervention), cardiomyopathy, myocarditis, pulmonary embolism, refractory ventricular tachycardia, shock during coronary intervention.
4. In-hospital cardiac arrest as a result of the cause stated in 'inclusion criteria 3'.
5. Those voluntarily consenting to the medical records and the data necessary for the study during the entire study period.

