### **15.3. Statistical analysis**

We aim to identify predictors of in-hospital death in patients who experience shock using binary logistic regression analysis. This type of analysis requires 10-15 events per independent variable, and with an expected mortality rate of about 40%, or approximately 400 deaths, we have sufficient events to study various risk factors. The goodness-of-fit of the model will be assessed using the C-statistic and Hosmer-Lemeshow test. In addition, we plan to compare the in-hospital death rate between patients with and without left ventricular assist devices using chi-square tests among those who receive a certain level of vasoactive drugs. We also aim to identify predictors of successful removal of the ECMO device and procedure-related complications such as bleeding, thrombosis, and limb ischemia using binary logistic regression analysis in patients who undergo ECMO. Finally, we plan to evaluate overall death over five years using Cox survival

analysis. We will assess the goodness-of-fit of the model by checking Schoenfeld's residuals and identify the hazard of each risk factor.

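### A device placed before shock is counted only if shock or arrest follows, yet section 15.3 keeps such patients in the device group whatever the timing of insertion

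*Protocol*

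**What the plan says.** Protocol section 11.2 gives two routes to a device. The usual one follows the "recommendations of the American Heart Association and the Korean Society of Cardiology when drugs are not effective". The other is for situations it calls exceptional: given "myocardial infarction with left ventricular wall motion abnormalities that are expected to result in cardiac arrest, the decision to insert IABP and ECMO more aggressively" rests with the operator. The second route is defined by an arrest that is expected. Nothing there requires shock to be present, and nothing says it is absent.

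Entry under section 9.1 needs criterion 2-1, "Systolic blood pressure is less than 90mmHg for more than 30 minutes despite the fluid therapy, or Use of pressure boosting agents is necessary", and criterion 2-2, signs of poor peripheral perfusion "or a person with pulmonary edema". Criterion 4 covers in-hospital arrest from a listed cause and is read here as an alternative way in. Section 11.1 likewise registers patients in shock.

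Section 15.3 plans to "compare the in-hospital death rate between patients with and without left ventricular assist devices" by chi-square test, among patients given some unspecified level of vasoactive drugs. It does not mention when the device was inserted relative to shock. Section 9.3 bases its power on this comparison, with rates of 0.3 (inserted) and 0.4 (not inserted).

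**The concern.** For most patients shock comes first and the device second, so registration does not depend on how well the device worked. If a device is placed before the entry criteria are met, the order is reversed. The device can then influence whether the patient is registered at all. A patient who stays stable does not enter, while one who deteriorates enters and counts in the device group.

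Adjustment for severity cannot repair this, because the missing patients are not in the data. It is therefore separate from the caveat in section 9.3 that the two groups are not on an equal footing, which concerns how ill the patients are. The comparison at stake is the one that the power statement supports, and it bears on the aim in section 6.1 of learning what IABP and ECMO achieve in cardiogenic shock.

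**Working it through.** **The plan's own figures.** Section 9.3 gives 400 device and 600 no-device patients, rates 0.3 and 0.4, an odds ratio of 1.56 and power of about 88%.

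- Odds ratio: (0.4/0.6)/(0.3/0.7) = 1.556.
- Power, with two-sided alpha 0.05 assumed because the Protocol states none: the Fleiss-Tytun-Ury correction with ratio r = 1.5 and difference d = 0.1 reduces the device group to 400 − (r+1)/(r·d) = 400 − 16.7 = 383.3. The power is then 88.9%. With 10% dropout (360 and 540) it is 85.3%, against the stated 84%.

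The stated figures are reproduced to within 2 points, and the present point leaves them unchanged. It concerns whom the 0.3 describes.

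**Who is registered, by timing of the device.**

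| Device placed | Later course | Registered? |
|---|---|---|
| After drugs failed in shock | Any | Yes |
| In shock, before drugs failed | Any | Yes, including when arrest is averted |
| Before shock | Shock or arrest follows | Yes, in the device group |
| Before shock | Neither follows | No |

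Only the last row is lost. The drug restriction in section 15.3 does not remove the third row: a patient who goes into shock despite the device is likely to receive vasoactive drugs and so to stay in the subset. Section 11.1 records the maximum drug dose without relating it to the time of insertion.

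**Size, as an illustration only.** The Protocol gives neither the share of pre-shock insertions nor how often they avert shock. Assume:

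- 400 registered device patients with mortality 0.30, the section 9.3 value for the whole inserted group;
- a share f of these 400 had the device placed before shock;
- a fraction s of all pre-shock insertions averts shock, so those patients are never registered;
- mortality is 0.05 in those never registered.

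The number missing is M = 400·f·s/(1 − s). Mortality with them included is (400 × 0.30 + 0.05·M)/(400 + M).

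| f | s | M | Mortality with the missing included | Registered mortality |
|---|---|---|---|---|
| 5% | 10% | 20 × 0.1/0.9 = 2.2 | 120.1/402.2 = 0.299 | 0.300 |
| 10% | 30% | 40 × 0.3/0.7 = 17.1 | 120.9/417.1 = 0.290 | 0.300 |
| 20% | 50% | 80 × 0.5/0.5 = 80 | 124/480 = 0.258 | 0.300 |
| 30% | 50% | 120 × 0.5/0.5 = 120 | 126/520 = 0.242 | 0.300 |

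The gap runs from 0.001 to 0.058, against a planned difference of 0.10.

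**The case against.** The strongest reply is that section 11.2 never says early insertion comes before shock. The contrast it draws is with waiting for drugs to fail, and the surrounding text (sections 6.2, 11.1 and 13) speaks of devices as treatment for shock. A reader might infer that the registry discards the successes of early insertion and sees only its failures. The documents do not support that. A patient already in shock who receives a device before drugs have failed is registered whatever the outcome, so an arrest averted in that patient is kept. Even patients who go into shock despite a pre-shock device are not all deaths.

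Two further replies carry weight. Section 11.2 calls these cases exceptional, so the number may be small. And the target disease in section 8 is cardiogenic shock, so leaving out patients who never had shock is within the registry's stated scope. Both limit the point without removing it. Patients with a device already in place when shock began still enter the device group, selected by the device having failed to prevent shock, and section 15.3 does not set them apart.

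It can also be said that subgrouping by timing belongs in the SAP, and that the e-CRF, which is not shown, may already capture insertion time. That is possible. But section 15.3 itself names the comparison and defines its groups by device status alone, so the correction belongs there.

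**Conclusion.** The point holds in a limited form. Section 11.2 leaves room for insertion before shock, sections 9.1 and 11.1 then admit those patients only if shock or arrest follows, and section 15.3 counts them as device patients, including within the vasoactive-drug subset. Relative to all patients who receive a device, registered device mortality is biased upward, provided that those in whom the device averts shock die less often than those registered. The amount cannot be computed from the Protocol. It is negligible if pre-shock insertion is rare, and material only if it is both common and often averts shock.

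The point does not extend to early insertion in established shock, and it does not show that the planned rates or the stated power are wrong. It is a clarification worth making because it is cheap and because section 15.3, as written, does not set these patients apart to show whether the effect is small.

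**What to change.** In section 15.3:

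- Restrict the device versus no-device comparison of in-hospital death to patients with no device in place at shock onset. Use the onset from which the flow chart already times lactate (footnote 5), or the in-hospital arrest for patients entering under criterion 4.
- Record insertion time relative to that onset.
- Report patients with a device already in place at onset as a separate descriptive group, outside both comparison groups.
- State that the comparison concerns device use in established shock.

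The cost is one timing field taken from the chart, a sentence or two in section 15.3, and a slightly smaller device group. Using the onset already in the flow chart avoids reconstructing from old records when each entry criterion was first met.

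The change does not separate use after drug failure from earlier use within shock, and it does not deal with the difference in severity that section 9.3 concedes. The clinical insertion rule in section 11.2 is unchanged.

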### 11.3. Follow-up schedule

Clinical follow-up: date of shock occurrence, 1, 6, 12M

## 12. Observation items/clinical examination items and observation/testing methods

### 12.1. Visit 1 (day of shock occurrence)

#### ① Written informed consent for patients enrolled

According to the scope of data collection, it is divided into prospective data collection subjects and retrospective data collection subjects.

- Prospective data collection subjects: The day of shock occurrence is after the IRB approval date
- Retrospective data collection subjects: The day of shock occurrence is before the IRB approval date

For prospective data collection subjects, before entering the clinical trial, the purpose and content of the trial should be explained in detail to the subject or legal guardian (in the case of a subject who cannot provide consent for the trial), and the written consent form should accurately record the signature dates of the subject and investigator. The original signed consent form is kept by the subject, and a copy is provided to the subject. If the subject is unable to consent on the day of the shock occurrence, the consent form is obtained from the representative of the accompanying subject. In this case, the principal investigator and sub-investigator must inform the subject or the subject's representative about the clinical trial as soon as possible and obtain consent to continue participating in the trial. If the subject recovers to a condition where consent can be given, the consent form is obtained from the subject.

For retrospective data collection subjects, only data corresponding to the study protocol are collected until IRB approval is obtained without written consent. However, among shock occurrence subjects before IRB approval, those who have obtained written consent are eligible for both prospective and retrospective data collection.

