| CPK, CK-MB, Troponin, NT-ProBNP                          | X                      |                   | X                   |                     |

1. There must be a signature from the patient or their legal guardian on the consent form. As this study is a retrospective and prospective registry study, data can be collected from patients who meet the selection criteria for either undergoing coronary angiography, insertion or non-insertion of a left ventricular assist device, after obtaining consent for access to medical records.
2. Age, sex, risk factors, medical history, clinical diagnosis, etc.
3. Investigate whether complications such as limb ischemia, stroke, sepsis, major bleeding events, vascular injury during insertion, and failure of left ventricular assist device insertion occurred.
4. CBC, Creatinine, Fasting glucose level, AST, ALT, T-bilirubin, LDH, Sodium
5. Lactate and ScVO2 are measured every 6 hours from the onset of shock, and then once a day until shock recovery.

\* Telephone (landline) interviews are also allowed for information gathering without the subjects having to visit the hospital.

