### (2) Background

Samsung Medical Center, Korea University Anam Hospital, Sejong General Hospital, Bucheon, Samsung Changwon Hospital, Ilsan Paik Hospital, Dankook University Medical Center, Konkuk University Medical Center, Chung-Ang University Hospital, Inha University Hospital, and Chungbuk National University Hospital are expected to participate, and considering the fact that 1,800 patients with acute myocardial infarction are being treated annually in 10 hospitals, about 5.5% of myocardial infarction patients progress to shock, which means that about 100 patients can be registered each year, and it is estimated that more than 100 patients can be registered due to other causes such as unstable angina, shock during procedures, cardiomyopathy, and myocarditis. Considering the five-year study period, it is estimated that more than 1,000 patients can be registered.

As for the group with left ventricular assist devices (LVADs) inserted, most of them are critically ill patients, so it should be noted that a comparison with the group without LVADs inserted cannot be made on an equal footing. However, other than that, sample size/power calculations for binomial proportions were applied using Fleiss, Tytun, and Ury (1980). With the above number of patients, it has about 88% statistical power to detect an odds ratio of 1.56 (inserted group = 0.3, non-inserted group = 0.4). However, if an expected dropout rate of about 10% is taken into account, the power is reduced to 84%.

In addition, considering that the group with LVADs inserted is significantly superior to the group without LVADs, a one-sided test is usually performed, and when adjusted, the power exceeds 90%. Therefore, it is expected that this clinical trial plan will be statistically and clinically successful when executed.

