## ⑦ Survival and death event investigation

## ⑧ Echocardiography

## ⑨ Coronary angiography for ischemic heart disease

## ⑩ Insertion of left ventricular assist device and investigation of complications

**12.2. Follow-up**

Visits are conducted at 1 month, 6 months, and 12 months after the shock event for the following tests and procedures. Information gathering through phone (landline contact) is also allowed without the subject's visit.

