### **15.2. Secondary Endpoints**

- 1) Death in 28 days
- 2) Death during follow-up
- 3) Death, myocardial infarction, stroke, re-admission due to heart failure during follow-up
- 4) Number of days of intensive care unit
- 5) Hospitalization days
- 6) Lactate 24 hour clearance
- 7) Successful removal of left ventricular assist device (IABP, ECMO)

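### For shocks before IRB approval, observation after approval depends on written consent, so deaths between approval and consent go unrecorded and consenters bring immortal time into the follow-up analyses

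*Protocol*

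**What the plan says.** Section 12.1 splits subjects by shock date: "Retrospective data collection subjects: The day of shock occurrence is before the IRB approval date". For these subjects, "only data corresponding to the study protocol are collected until IRB approval is obtained without written consent". It then makes an exception: among them, "those who have obtained written consent are eligible for both prospective and retrospective data collection". Read together, the two sentences give pre-approval shocks two lengths of observation, one ending at approval and one continuing past it.

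Section 12.2 sets the schedule without that distinction: "Visits are conducted at 1 month, 6 months, and 12 months after the shock event". Section 15.2 lists death within 28 days, "Death during follow-up" and a composite over follow-up as secondary endpoints. Section 15.3 adds a Cox analysis of overall death over five years and mentions neither a cut-off at approval nor delayed entry.

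Footnote 1 of the flow chart says "There must be a signature from the patient or their legal guardian on the consent form", so a guardian may sign for a living patient who cannot. Section 12.1 describes consent by a representative only for prospective subjects. No route is given for a subject who dies after approval and before anyone has signed.

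**The concern.** The collection rule decides which deaths can be seen. A death before approval falls within the consent-free data and is captured. A death after approval is captured only if consent was already in place. A retrospective subject who consents some weeks after approval must have been alive until then, so those weeks carry no risk of a recorded death. A subject who died in the same weeks leaves no record of it and appears as someone last seen alive at approval.

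If consenters are counted at risk from the shock date, the risk set is inflated by time in which they could not have been seen to die. If subjects cut off at approval are treated as alive at 6 or 12 months, deaths are lost outright. Either would distort the follow-up mortality that the registry sets out to describe, and would mix survivors' time into the Cox hazard ratios.

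**Working it through.** **Planned rate.** Section 9.3 gives 1,800 infarctions a year and 5.5% progressing to shock: 1,800 × 0.055 = 99, which is its figure of about 100. Adding about 100 from other causes (read as annual) gives 200 a year. Over five years, 200 × 5 = 1,000, which agrees with "Considering the five-year study period, it is estimated that more than 1,000 patients can be registered" and supports the annual reading.

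**Subjects exposed.**
- 12-month endpoints: shocks in the year before approval, 200 × 1 = 200, or 20% of 1,000.
- Five-year Cox analysis: section 11.1 puts two and a half years of registration before approval, so 200 × 2.5 = 500, which is every retrospective subject.
- Shocks within 28 days of approval: 200 × 28/365 = 15.
- Shocks within 90 days of approval: 200 × 90/365 = 49.

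The 15 and 49 are upper bounds on missing 28-day or discharge status. Subjects who died or left hospital before approval, and those who consent, have known status. The 90 days is illustrative, because the protocol gives no length of stay.

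**Simulation of 12-month mortality, shocks in the last pre-approval year.** From the protocol: 40% early mortality (section 15.3). Assumed:
- shocks uniform over 365 days
- early deaths at a mean of 10 days, capped at 60
- later mortality m = 10% or 20%, with daily hazard −ln(1 − m)/365
- exponential gap from approval to consent, mean 0, 30 or 90 days
- consent share 30%, 70% or 100%
- hazard ratio of non-consenters 1 or 2
- 60,000 subjects per scenario

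Check on the true values: 0.40 + 0.60 × 0.10 = 46.0% and 0.40 + 0.60 × 0.20 = 52.0%, against simulated values of about 46% and 52%.

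Selected results, hazard ratio 1 (12-month mortality, %):

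| m | Mean gap (days) | Consent share | True | Kaplan-Meier, at risk from shock | Kaplan-Meier, re-entry at consent | Known status only | Unknown = alive |
|---|---|---|---|---|---|---|---|
| 10% | 30 | 30% | 46.1 | 45.6 | 46.1 | 72.8 | 42.8 |
| 20% | 0 | 70% | 51.5 | 51.5 | 51.5 | 59.4 | 49.6 |
| 20% | 30 | 70% | 51.7 | 50.7 | 51.8 | 59.0 | 48.5 |
| 20% | 90 | 70% | 51.9 | 49.8 | 51.9 | 58.8 | 47.6 |
| 20% | 90 | 100% | 51.9 | 49.3 | 51.9 | 50.6 | 48.7 |

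Across all scenarios:
- **Deaths in the gap.** For mean gaps of 30-90 days, 2.4 to 8.7 deaths per 200 subjects fall between approval and the actual or would-be consent date.
- **Kaplan-Meier with consenters at risk from shock.** Hazard ratio 1, gaps of 30-90 days: understated by 0.5 (46.1 − 45.6) to 2.6 (51.9 − 49.3) points. Hazard ratio 2: by up to 3.2 points (54.7 − 51.5). No gap and hazard ratio 1: no bias beyond simulation error.
- **Kaplan-Meier with re-entry at consent.** Hazard ratio 1: bias about zero. Hazard ratio 2: still understated, by up to 2.2 points (58.1 − 55.9).
- **Unknown counted as alive.** Understated by about 1 to 9 points whenever consent is incomplete or there is a gap.
- **Known status only.** Overstated when consent is incomplete (70% consent: 53.5-60.1% against a true 45.9-54.7%), because pre-approval deaths stay in while non-consenting survivors drop out. With 100% consent and a gap it is understated by about 1 point.
- **Consenters only.** 3-13% against a true 46-58%.

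**Whole registry.** With 20% of subjects exposed, 0.2 × 0.5 = 0.1 and 0.2 × 2.6 = 0.5 points of 12-month mortality, as a rough scaling.

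**The case against.** The strongest reply is that a cut-off at a calendar date is ordinary administrative censoring, which Cox regression handles, and that delayed entry is the sort of detail a statistical analysis plan supplies. That plan is not at hand and may contain it. The reply holds for the estimator and for subjects who never consent, provided their risk is similar. It does not hold for the collection rule. That rule is in the protocol, and no later analysis can recover a death in the gap that was never collected. Delayed entry is needed because the rule makes continuation conditional on surviving to consent, which is not administrative censoring.

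It can also be said that the 1, 6 and 12 month visits in section 11.1 follow consent and enrolment, so the narrower scope for non-consented subjects is a limit on data use and not a contradiction. That is fair. The point rests on the selective observation, not on a clash of wording.

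Stronger readings that a reader might infer, and why the protocol does not support them:
- *Follow-up mortality must be understated.* The direction depends on the estimator and can reverse. Nothing in the protocol says that subjects cut off at approval will be counted as survivors.
- *All retrospective deaths are lost unless the subject survived to consent.* Deaths before approval are collected without consent, and a guardian may sign for a living patient.
- *The primary endpoint is missing for 15 or 49 subjects.* These are counts of shocks, not of missing outcomes. Patients in hospital at approval are also the easiest to approach for consent.

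**Conclusion.** The point holds as a selection problem in post-approval follow-up of pre-approval shocks. It affects the follow-up death and composite endpoints for about 200 subjects on the 12-month schedule, and all retrospective subjects (about 500) in the five-year Cox analysis. With consenters at risk from shock and equal risk in non-consenters, 12-month mortality in the last pre-approval year is understated by about 0.5-2.6 points. That is small for the registry as a whole. The figures rest on the assumed consent gap, consent share and later mortality, none of which the protocol gives. The effect on the five-year analysis was not computed.

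In-hospital death is affected only for non-consented subjects still in hospital at approval. A reader might infer wider survivor selection from inclusion criterion 5 in section 9.1 ("Those voluntarily consenting to the medical records and the data necessary for the study during the entire study period"), which carries no exemption for retrospective subjects. If it were applied to them, selection would be much stronger and would reach the primary endpoint. Section 12.1, the more specific text, waives written consent for them, so this is not the working reading. The criterion, flow chart footnote 1 and section 12.1 should still be reconciled.

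**What to change.** In sections 12.1 and 15.3, state that:
1. Retrospective subjects without written consent are censored at their site's IRB approval date. They are never counted as alive at a later visit.
2. Consented subjects with shock before approval contribute person-time from shock to approval, leave the risk set, and re-enter only at the consent date. This applies to the Cox analysis and to the other follow-up death and composite analyses.

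The cost is protocol wording and three dates per subject: shock, site approval and consent. No subject is lost. Intervals widen slightly because the gap no longer counts as time at risk. Some bias remains if non-consenters fare worse (up to about 2.2 points in the last pre-approval year at twice the hazard), so the number of non-consented subjects alive at approval should be reported.

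Closing non-consented entry some weeks before approval, for example 90 days, may look like a remedy but should not be adopted. It would discard in-hospital deaths that are fully observed before approval, while keeping consented subjects who mostly had to be alive at approval. That would put survivor selection into the primary endpoint.
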